#### 4.8.2 Missing data

We will make every effort to minimize missing data. Trial enrollment and the fidelity of follow-up procedures will be reviewed during monthly conference calls. In our pilot trial of the Chest Pain Choice decision aid only 2% of patients were unable to be contacted by phone at 30 days for follow-up, indicating that study data were 98% complete. A study biostatistician will conduct frequency reports to assess for missing data, and the study team, which is experienced in conducting multicenter trials, will trouble shoot any problems encountered. Patients with missing outcome data will not be included in the assessment of that outcome. We will report rates of missing data for each outcome by study arm and known reasons for missing data. For data elements that are used to adjust study comparisons we will use multiple imputation to account for any that are missing at random (MAR).

#### 4.8.3 Sample Size Estimation

Patient knowledge will be the primary outcome, as it was considered to be the most important endpoint by our patient representatives on the ED Patient Advisory Council. In order for the study findings to maximally impact practice and policy, however, we will need to be adequately powered to detect differences in the outcomes of interest to each of the stakeholders.

Accounting for a lost to follow-up rate of as high as 5% (there was 2% lost to follow-up in our pilot trial), approximately 75 clinicians (assuming an average of 15 clinicians/site) will enroll 950 patients. This will provide the following power to detect differences in each of the patient and stakeholder-important outcomes (using a 2-sided hypothesis test and an alpha of 0.05):

| Outcome (n = 950)                                                                                | Usual Care* | Decision Aid* | Difference | Power |
|--------------------------------------------------------------------------------------------------|-------------|---------------|------------|-------|
| Parent knowledge                                                                          | 44%         | 60%           | 16%        | >99%  |
| Parent engagement in the decision making process                                          | 7.0 (5.5)   | 27.0 (8.2)    | 20.0       | >99%  |
| Decisional conflict †                                                                     | 36 (19)     | 21 (21)       | 15         | >99%  |
| Trust in the physician                                                                    | 79 (20.0)   | 84 (20.0)     | 4.1        | 86%   |
| Parent satisfaction with the decision made (% agree or strongly agree they are satisfied) | 70.0 (26)   | 80 (26.0)     | 10.0       | >99%  |
| Safety (clinically-important traumatic brain injury) ‡                                    | 0.9%        | 0.9%          | 0%         | 82.5% |
| Proportion of children who undergo head CT §                                              | 49%         | 34%           | 15%        | 95%   |
| Healthcare utilization                                                                    | 8.3 (0.8)   | 6.8 (0.7)     | 1.5        | >99%  |

\*Estimates were determined from our completed randomized trial.

†Lower decision conflict scores indicate less conflict experienced by patients related to feeling uninformed.  
‡ Noninferiority, 1-sided test with alpha = 0.05 with a maximum difference of 2%. Baseline rates determined from the PECARN prediction rule study.  
§ Obtained from the rate of CT in the moderate risk group of patients in the PECARN prediction rule study.

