|----------------------------------------------------|------------------------------------|----------------------------------|-------------------------------------------|
| Patient knowledge                           |                                    |                                  |                                           |
| 6 Knowledge Questions                              | 3.6 (3.4, 3.9)                     | 3.0 (2.7, 3.2)                   | 0.67 (0.34, 1.0)                          |
| Correctly assessed 45-day risk for ACS             | 24 (25%)                           | 1 (1%)                           | <.0001                                    |
| Decisional Conflict and Trust               |                                    |                                  |                                           |
| Decisional conflict scale                          | 22.3 (18.1, 26.4)                  | 35.9 (32.2, 39.6)                | -13.6 (-19.1, -8.1)                       |
| Trust in physician                                 | 83.4 (79.4, 87.3)                  | 79.3 (75.4, 83.2)                | 4.1 (-1.4, 9.6)                           |
| Patient participation                       |                                    |                                  |                                           |
| Patient engagement by the clinician (OPTION scale) | 51.4 (49.7, 53.0)                  | 32.0 (31.0, 33.1)                | 19.3 (17.4, 21.2)                         |

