## **4.3 Study Setting and Participation**

### **4.3.1 Emergency Department Setting**

The locations include 4 diverse hospital EDs across Minnesota – (1) Mayo Clinic in Rochester, MN (academic ED that serves a largely rural population); (2) University of Minnesota Masonic Children’s Hospital in Minneapolis, MN (academic ED that serves a largely urban population); (3) Children’s Hospital and Clinics of Minnesota, Minneapolis ED; and (4) Children’s Hospital and Clinics of Minnesota, St. Paul ED (2 pediatric community EDs that serve largely urban populations) and 3 hospitals outside the state, (1) University of California Davis Children's Hospital, Sacramento, CA (academic ED that serves a largely urban population) (2) Children’s Nationwide Hospital in Columbus, Ohio (3) Boston Children’s Hospital in Boston, Massachusetts.

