#### 4.4 Registration/Randomization Procedures

The flow and process of identifying eligible patients for enrollment in the study is depicted in **Appendix 2**.

Given the relatively limited number of pediatric clinicians at each site and the great degree of familiarity with the PECARN head CT decision rules across the specialty of pediatric emergency medicine, randomizing at the patient level is associated with a significant risk of contamination of the intervention. As such, we will randomize at the clinician level to limit contamination.

Informed consent will be obtained from clinicians at each site prior to enrollment of that clinician's parent/child dyad. After clinician consent is completed, the site study coordinator will contact the statistical team ([[name]/[name]](#)) with enrollment information via email. The statistician will centrally randomize the clinician and communicate that to the site principle investigator and study coordinator.

Informed consent will also be obtained from the parent/guardian of a child with minor head trauma. The parent must provide signed and dated consent for the use of their Protected Health Information (this may be incorporated into the informed consent document). Prior to registering a parent(s) to the study, all of the eligibility criteria on the eligibility checklist must have been met. **No waivers or exemptions to any eligibility criteria are permitted.** All eligibility criteria must be fully documented on the case report form and subsequently entered into the study database.

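### Power table, trust in the physician: the printed means differ by 5 points, the printed difference is 4.1, and the 86% power fits 4.1 only with almost no clustering

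*Protocol*

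**What the plan says.** Protocol section 4.8.3 bases its power table on the statement that "approximately 75 clinicians (assuming an average of 15 clinicians/site) will enroll 950 patients. This will provide the following power", after allowing for up to 5% loss to follow-up and "using a 2-sided hypothesis test and an alpha of 0.05". It adds that the trial needs adequate power for the outcomes that matter to each stakeholder. A footnote attributes the planning values to the completed pilot trial.

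The trust row reads, in the order usual care, decision aid, difference, power: "79 (20.0) | 84 (20.0) | 4.1 | 86" (per cent). Table 1 in section 3.2 gives the pilot result for the same scale, decision aid first: "83.4 (79.4, 87.3) | 79.3 (75.4, 83.2) | 4.1 (-1.4, 9.6" as the confidence limits.

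Section 4.4 fixes the unit of randomization: "we will randomize at the clinician level to limit contamination". Section 4.8.1 adjusts the comparisons for clustering by clinician. Neither an ICC nor a design effect is given.

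Section 4.3.1 opens its site list with "The locations include 4 diverse hospital EDs across Minnesota" and then adds three hospitals in other states, seven in all.

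**The concern.** The trust row carries two effect sizes and one power. The two means give 84 − 79 = 5.0 and the difference column gives 4.1. A reader cannot tell which one the 86% belongs to, and under clinician randomization the two have clearly different power.

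Of the superiority comparisons in the table, trust has the lowest stated power, so it has the least room for error. If the 86% belongs to 5.0 points, the trial is less able to detect the effect seen in the pilot than the row suggests, and a null trust result could be read as stronger evidence of no effect than it is. The missing ICC and the mismatch between clinician and site numbers mean that the reader cannot settle this from the section itself.

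**Working it through.** **Inputs.** Two-sided alpha 0.05, SD 20, 950 patients, 5% loss (902.5 analysed), 75 clinicians (all section 4.8.3); 1:1 allocation (section 4.8.4). Mean cluster size m = 950/75 = 12.67, or 902.5/75 = 12.03 after loss. The ICC is not in the protocol and is varied below.

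**Formula.** Power = Φ(δ / (SD·√(2·DE/n)) − 1.96), with n per arm and DE = 1 + (m − 1)·ICC.

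**Step 1: where the printed 86% can come from.**
- 4.1 points, no clustering, n = 475: SE = 20·√(2/475) = 1.298; Φ(3.159 − 1.96) = 88.5%. With n = 451.25: SE = 1.331; Φ(3.079 − 1.96) = about 87%.
- 5.0 points, ICC 0.05, n = 475: DE = 1 + 11.67 × 0.05 = 1.583; SE = 1.633; Φ(3.062 − 1.96) = 86.5%. With n = 451.25: DE = 1.552; SE = 1.659; 85.4%.
- 4.1 points with a very small ICC: 86% is reached at ICC of about 0.007 (950 patients) or 0.002 (902.5).

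**Step 2: what the other rows imply about clustering.**
- Safety (0.9% in both arms, margin 2%, one-sided 0.05). Without clustering: SE = √(2 × 0.009 × 0.991/475) = 0.00613; Φ(0.02/0.00613 − 1.645) = 94.7% (93.8% with 902.5). The table states 82.5%. The design effect that gives 82.5% is 1.60 (950) or 1.52 (902.5), so ICC = 0.60/11.67 or 0.52/11.03, about 0.05.
- Head CT (49% vs 34%). Without clustering, the two-proportion z-test with pooled null variance gives 99.7% (950) or 99.6% (902.5). The table states 95%. The implied design effect is 1.71 or 1.63, an ICC of about 0.06.

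These two rows therefore appear to include clustering.

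**Step 3: power for trust with 75 clinicians.** Each cell gives 950 patients, then 902.5.

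| ICC | 4.1 points | 5.0 points |
|---|---|---|
| 0 | 88.5%, 87% | 97.1%, 96.4% |
| 0.01 | 84.8%, 83.2% | 95.4%, 94.6% |
| 0.02 | 81.2%, 79.6% | 93.4%, 92.5% |
| 0.05 | 70.9%, 69.6% | 86.5%, 85.4% |
| 0.10 | 57.4%, 56.5% | 74.5%, 73.5% |

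At the design effect implied by the head CT row, power for 4.1 points is 67.5%.

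**Step 4: number of clinicians.** 75/15 = 5 sites, but seven are listed. Seven sites at 15 would be 105 clinicians. At ICC 0.05, m = 9.05 and DE = 1.402 (950), or m = 8.60 and DE = 1.380 (902.5). Power for 4.1 points is then 76.1% or 74.6%, and for 5.0 points 90.2% or 89.2%.

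**Step 5: do other rows need to change?** Table 1 gives a knowledge difference of 0.67 of 6 questions, about 11 points. Its interval (0.34 to 1.0) implies an SD of (0.33/1.96)/√(1/101 + 1/103) = 1.20 questions, about 20 points. At ICC 0.05 and 300 effective patients per arm, 11/(20·√(2/300)) = 6.7, so power exceeds 99%. For decisional conflict, the Table 1 difference of 13.6 with the larger printed SD of 21 gives 13.6/(21·√(2/300)) = 7.9, again above 99%.

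**The case against.** The best defence is that the 86% may be right and only one cell wrong. The printed means with ICC 0.05 give 85.4% to 86.5%, which brackets the stated figure and agrees with the clustering in the safety and head CT rows. On that reading the power belongs to 5.0 points, and the difference column was filled with the pilot value. This stands as the most likely explanation. The row still contradicts itself, but it means that 4.1 cannot be presumed to be the planned difference.

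A reader might infer that true power for trust is about 70%. The documents do not support that as a fact. It needs ICC 0.05 for this scale, and that value is back-calculated from two binary outcomes. ICCs differ between outcomes, so trust could have a smaller one: 4.1 points gives 86% at ICC of about 0.007 with 75 clinicians, or at 0.01 with 105 clinicians and 950 patients.

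A reader might also infer that this row simply ignored clustering. That is possible (about 87% with 902.5 analysed), but it is one explanation among several.

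Finally, one might want the knowledge and decisional conflict rows replaced by Table 1 values, since 44% and 15 do not match 3.0/6 = 50% and 13.6. The planned decision-aid knowledge value of 60% does equal 3.6/6, the engagement row also departs from Table 1, and power stays above 99% with the Table 1 inputs. At most, the source of these values should be stated.

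**Conclusion.** The trust row is wrong as written: its means, its difference and its power cannot all belong to one calculation. If 5.0 points was planned, 86% is about right at ICC 0.05 and the difference cell is wrong. If 4.1 was planned, 86% requires almost no clustering, and the clustering implied elsewhere in the table would put power near 70%. Because no ICC is stated, the supportable statement is a range for 4.1 points: from 83-85% at ICC 0.01 to 56-57% at ICC 0.10 with 75 clinicians. These figures assume equal cluster sizes and a normal approximation.

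Severity is minor. Knowledge is the primary outcome and is unaffected, trust is not named in the hypothesis in section 1.0, and section 6.2 plans no early stopping for benefit or futility. The row is still worth correcting, because section 4.8.3 claims adequate power for each stakeholder's outcomes.

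**What to change.** - Make the trust row consistent. Either print a difference of 5.0 with its clustered power (about 86% at ICC 0.05 and 75 clinicians) and note that this exceeds the pilot's 4.1, or print the pilot means and a difference of 4.1 with its clustered power (about 70% under the same assumptions). The sponsor must say which was planned.
- State the ICC assumed (by outcome if it differs), the number of clinicians and the analysed number behind the table.
- Reconcile 75 clinicians at 15 per site with the seven sites in section 4.3.1, and recompute the trust power for the settled count. With 105 clinicians and ICC 0.05 it would be about 75-76% for 4.1 points and 89-90% for 5.0.
- Leave the knowledge and decisional conflict rows as they are; a note on the source of those inputs would suffice.

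The cost is a text correction. No patients are added and no analysis changes. One stated power may become less favourable.

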Satisfaction: We will assess parents' satisfaction by asking 5 questions regarding the acceptability and satisfaction regarding the way information was shared during the encounter using a 7-point Likert .

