#### 4.8.4 Allocation process

Clinicians will be randomized at the beginning of the study and, if necessary, when first treating an eligible patient. Clinician randomization will be stratified by study site and according to whether they are pediatric emergency clinicians or not. To maintain balance the randomization algorithm utilized will balance across the stratification factors dynamically as clinicians are enrolled.

Randomization will be assigned on a 1:1 basis across arms. Though we will not be able to blind parents and clinicians to use of the decision aid, we will blind the investigators and all nonclinical stakeholders to study arm.

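### The parent satisfaction row in 4.8.3 is labelled as a percentage but powered as a mean with SD 26; as a yes/no outcome its power is at most about 95%, not >99%

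*Protocol*

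**What the plan says.** The power table in Protocol 4.8.3 labels the row "Parent satisfaction with the decision made (% agree or strongly agree they are satisfied". The entries and stated power are "70.0 (26) | 80 (26.0) | 10.0 | >99"%. Engagement, decisional conflict, trust and utilization are entered the same way, as a value with a second figure in parentheses. Safety and head CT, which are plain proportions of children, carry a percent sign and no SD.

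Section 4.7.2 describes the measure as "asking 5 questions regarding the acceptability and satisfaction regarding the way information was shared during the encounter using a 7-point Likert" scale. It gives no cut-point for agreement, no rule for combining the five items and no 0-100 scoring. Its subject is the sharing of information, whereas the table row concerns the decision made.

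The remaining design inputs in 4.8.3 and 4.8.4 are "using a 2-sided hypothesis test and an alpha of 0.05", "approximately 75 clinicians (assuming an average of 15 clinicians/site) will enroll 950 patients", and "Randomization will be assigned on a 1:1 basis across arms". Section 4.8.1 assigns t-tests to continuous outcomes and chi-square tests to dichotomous ones, adjusted for clustering by clinician. No ICC or design effect is stated anywhere.

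**The concern.** The label and the numbers describe different kinds of variable. A yes/no response at 70% and 80% has SDs of about 46 and 40 percentage points, so an SD of 26 cannot belong to it. The power beside the label was evidently calculated for something else.

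Satisfaction is named in the trial's hypothesis (section 1.0), and 4.8.3 presents the table as evidence that the trial is adequately powered for the outcomes each stakeholder cares about. A reader who takes the label at face value is given a power that the named endpoint does not have. Because 4.8.1 chooses the test by outcome type, the form of the endpoint also decides the test. With the form unsettled, the choice between a mean and a dichotomy could be made after the data are seen.

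**Working it through.** **Inputs.** N = 950, 1:1, so n = 475 per arm. Two-sided alpha 0.05 (z = 1.960). Values 70 and 80, SD 26. 75 clinicians, so the mean cluster size is 950/75 = 12.67. All are from 4.8.3 and 4.8.4. The ICC is not in the protocol; the values below are assumptions.

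**1. The stated figure, as a comparison of means.** Power = Φ(δ / (σ√(2/n)) − 1.960).
- 10 / (26 × √(2/475)) = 10 / 1.687 = 5.927; minus 1.960 = 3.967; power 99.996%.
- 99% power needs δ/SE = 1.960 + 2.326 = 4.286, that is, 2 × (4.286 × 26/10)² ≈ 248 per arm. The design effect may therefore reach 475/248.4 ≈ 1.91 before power drops below 99%.

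So >99% is right for a mean with SD 26, even with moderate clustering.

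**2. The endpoint as labelled, 70% against 80%.** SDs: √(0.70 × 0.30) = 0.458 and √(0.80 × 0.20) = 0.400. Power = Φ((d√n − 1.960√(2p̄q̄)) / √(p₁q₁ + p₂q₂)), with d = 0.10, p̄ = 0.75, √(2p̄q̄) = √0.375 = 0.612 and √(0.21 + 0.16) = 0.608.
- n = 475: (2.179 − 1.200) / 0.608 = 1.610; power 94.6%. With the unpooled variance throughout it is 94.8%.
- One-sided at 0.05: 97.3%, still below 99%.
- n for 99%: (1.200 + 2.326 × 0.608)² / 0.10² ≈ 684 per arm, before any clustering.

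**3. Clustering.** DE = 1 + (12.67 − 1) × ICC, effective n = 475/DE. Equal cluster sizes are assumed.

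| Assumed ICC | DE | Power, 70% vs 80% | Power, mean with SD 26 |
|---|---|---|---|
| 0 | 1.00 | 94.6% | >99.9% |
| 0.01 | 1.117 | 92.2% | 99.99% |
| 0.02 | 1.233 | 89.5% | 99.96% |
| 0.05 | 1.583 | 80.9% | 99.7% |
| 0.10 | 2.167 | 67.8% | 98.1% |

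**4. Do the table's other rows reveal the ICC used?** Solving for the design effect that reproduces each stated power at N = 950, and applying it to 70% against 80%:

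| Row | Implied DE | Satisfaction power as a percentage |
|---|---|---|
| Safety (82.5%) | 1.60 | 80.5% |
| Trust, read as 79 vs 84 (86%) | 1.61 | 80.4% |
| Head CT (95%) | 1.71 | 77.8% |
| Trust, printed difference 4.1 (86%) | 1.08 | 93.0% |

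The rows do not agree on one value. All of them leave the labelled endpoint below 99%.

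**The case against.** The best defence is that the power is correct and only the label is wrong. The entries are in mean (SD) form, >99% reproduces for them with room for clustering, and 4.7.2 describes Likert items with no dichotomy. Item scoring may also be set out in an analysis plan that is not shown. This is a fair explanation. It does not clear the row, because the label is part of the current text and 4.7.2 defines no score on which 70, 80 and 26 can be read.

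A second defence is that the percentage could be each parent's share of the five items endorsed, as 4.7.2 scores knowledge. At 70% agreement such a share has an SD of √(0.21/5) ≈ 20 points if items are independent, and √(0.042 × 1.6) ≈ 26 with an inter-item correlation of 0.15. That is possible, but the protocol does not say it. The SDs of 46 and 40 apply only to one yes/no response per parent.

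Two stronger conclusions are tempting. One is that the trial has only about 81% power for satisfaction. That needs an ICC of 0.05, which the protocol never states, and the other rows point to anything from about 78% to 93%. The other is that treating the five items as a 0-100 mean makes >99% correct. Nothing shows that such a mean has SD 26 or a 10-point difference: the table footnote credits the earlier chest-pain trial, but Table 1 in section 3.2 has no satisfaction row.

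Nor does the 5% loss to follow-up clearly reduce this outcome, since the parent survey follows the discussion directly (section 4.6). Taking it off 950 would give 93.6% unclustered.

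**Conclusion.** The point holds as an inconsistency that makes a stated power wrong for the endpoint as named. Read as the proportion of parents who agree, 70% against 80% with 475 per arm has at most about 95% power. That bound needs no assumption about clustering. Any clustered figure is conditional: about 92% to 68% for ICCs of 0.01 to 0.10.

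The documents do not show that the trial is underpowered for satisfaction, or that a chi-square test will be used, because 4.8.1 does not classify this outcome. If a continuous score was meant and the inputs belong to it, >99% stands and only the wording is wrong. Knowledge is the primary outcome, and nothing here changes the sample size of 950. The correction is still worth making, because the outcome is in the hypothesis and its form determines its test.

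**What to change.** Make the row label and inputs in 4.8.3 and the definition in 4.7.2 describe one endpoint, including whether it concerns the decision made or the sharing of information.

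- **If it is a percentage of parents:** remove the SDs, state which item or items and which of the seven response levels count as agreement, and restate the power as at most 95% unclustered. Add the clustered value with its ICC, for example about 81% at ICC 0.05.
- **If it is a continuous score:** remove the percent-agreeing wording from the label, state how the five items are combined and scaled, and keep >99% only if the 10-point difference and SD of 26 apply to that score. Give their source.

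The cost is one table row and a sentence or two in 4.7.2. The design and sample size do not change.
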